### Recruitment and randomization

Twelve eligible primary care clinics, each with a team consisting of a physician, psychologist, and social worker, are enrolled to obtain the sample. The clinics are invited through an official request to the Maule Region health administration. Once authorized by their directors, the selected primary care clinics (Centros de Salud Familiar) participate. Clinics are matched based on similar average socioeconomic and educational characteristics, ensuring no cross-contamination between patients from control and intervention clinics. Data from 2019 on socioeconomic level, adult population, and patient income are used to match clinic pairs.
^
19
^

A separate researcher, not part of the training team, create a list of clinic pairs, with similar characteristics in Excel and assign each clinic a number (1 or 2). Clinics are then assigned to either the intervention or control group using a pseudo-random algorithm (randi(2, [1 12]), which generates a 12-by-1 matrix of random integers between 1 and 2) in Matlab (MathWorks, Natick, MA, USA, RRID).

Finally, this researcher assigns number codes to the intervention and control groups. A different group of researchers, blinded to the group assignments, performs data collection and analysis using these codes. Patients who begin treatment for depression at their respective primary care clinics are informed of the study and invited to participate by a designated member of the primary care team. Those who agree to participate provide their telephone numbers, and researchers, blinded to group assignments, contact them to obtain informed consent and administer the questionnaires. An alphanumeric code is assigned to each intervention arm, clinic, and patient. Consequently, participants, outcome assessors, and data analysts remain blinded to the intervention allocation.

Patient recruitment begin on March 1, 2022 and conclude by November 2022.

### Participant timeline

**Table 1. T1:** Timeline of health care teams and patients’ measurements and actions as specified in the protocol.

Time	Study						
	Teams			Patients			
	Pre	Training	Post	Enroll	Study		
					0	3 m	6 m
**Intervention**		X					
**Enrollment**				X			
*Informed Consent*				X			
*Eligibility*				X			
**Evaluations**							
*PHQ*					X	X	X
*GAD-7*					X	X	X
*OQ-45*					X	X	X
*ERS*					X	X	X
*Adherence Scale*						X	X
*GSES*	X		X				

Abbreviations: PHQ, Patient Health Questionnaire; GAD-7, General Anxiety Disorder Scale-7; OQ-45, Outcome questionnaire 45; ERS, Emotion regulation scale; GSES, General self-efficacy scale.

### Outcomes measures

**
*Primary outcome*
**

*Change in depressive symptoms*

Differences in depressive symptoms between baseline and follow-up across the two study arms are assessed at baseline, three months, and six months, as shown in the participants’ timeline (
Table 1), using the Patient Health Questionnaire validated in Chile. This questionnaire is a 9-item self-report survey that uses a 4-point Likert scale to screen for the presence of MD and monitor treatment effects. The total score ranges from 0 to 27, with higher scores indicating greater severity of depression. The presence of five or more symptoms on more than half of the days in the past two weeks suggests major depresson (
Table 1), using the Patient Health Questionnaire validated in Chile.
^
23
^ This questionnaire is a 9-item self-report survey that uses a 4-point Likert scale to screen for the presence of MD and monitor treatment effects. The total score ranges from 0 to 27, and a greater score means a greater severity of depression. The presence of five or more symptoms in at more than half the days in the last two weeks suggests MD.

**
*Secondary outcomes*
**

*Change in anxiety symptoms*

Difference in anxiety symptoms between baseline and follow up across the two arms of the study will be assessed at baseline and three and six months (
Table 1) by the Spanish validated version of the generalized anxiety disorder scale-7 (GAD-7).
^
24
^ The GAD-7 is a 7-item self-report survey that uses a 3-point Likert scale to screen for generalized anxiety disorder quantify symptom severity. The total score ranges from 0 to 21 points, and greater scores mean greater severity of anxiety.

*Change in interpersonal dysfunction and social role difficulties*

Difference in functional impairment in interpersonal and social areas between baseline and follow-up across the two arms of the study will be assessed at baseline, at three and at six months (
Table 1) by the subscales of the interpersonal functioning, and social role included in the Outcome Questionnaire 45 (OQ-45).
^
25
^ The OQ-45 has a 45-item self-report survey that uses a 4-point Likert scale originally developed to monitor patient progress during therapy and after termination. The OQ-45 comprises the subscales of symptom distress, interpersonal relations, and social role. The interpersonal relations subscale includes 12 items addressing loneliness, conflict with others, and marriage and family difficulties, with scores that range from 0 to 48. The social scale consists of nine items tapping into difficulties in the workplace, school or home duties, with scores that range from 0 to 36 points. Greater scores mean worse interpersonal and social functioning.

*Change in emotion regulation*

Difference in the difficulties in emotion regulation between baseline and follow-up across the two arms of the study will be assesed at baseline, three and six months (
Table 1) by the emotion regulation scale (ERS) validated in Spanish with cutoff scores for the Chilean population.
^
26
^ ERS contains five subscales addressing emotional rejection, dysregulation, interference, inattention, and confusion. This scale is a 28-item self-report survey that uses a 5-point Likert scale. The scores range from 0 to 140 points, and greater scores indicate increased difficulties with emotional regulation.

*Therapeutic adherence*

Difference in the adherence to treatment between the two arms of the study will be assessed at three and six months (
Table 1) by the therapeutic adherence scale,
^
27
^ a 21-item self-reported survey to measure the percentage that patients assign the effectiveness of each behavior. A score of 100 represents the highest adherence possible.

**
*Other outcomes*
**

*Self-efficacy of the primary care teams*

The self-efficacy of the primary care team, in implementing the study model, will be evaluated at baseline and after training (
Table 1) by the general self-efficacy scale (GSES) validated in Chile.
^
28
^ The GSES is a 10-item self-report survey that uses a 7-point Likert scale to measure self-efficacy. Thus, greater scores mean greater self-efficacy.

### Data collection, management and monitoring

The study complies with all local research governance requirements for human data collection. The data from different instruments are entered into a virtual worksheet located on a secure website (
https://www.surveymonkey.com/) using a tablet. Each evaluator enters the data using a password, leaving no information on the devices. The data are checked for correct entry every day and downloaded to the PI’s personal computer, which is password-protected and located in a locked office. All data are entered with an alphanumeric code to prevent participant identification.

The data monitoring is performed by the research team in charge of data collection, which meets every two weeks to evaluate the trial progression and data collection. A different research team, responsible for data analysis, checks the collected data and performs preliminary data analysis to assess the progression of data collection.

### Monitoring

Patients are first monitored by their respective primary care teams as part of their treatment. If risk situations such as serious suicide risk, psychosis, or adverse effects of medications are detected during evaluations by the residents, they notify the researchers responsible for data collection, who, in turn, inform the primary care teams. The healthcare teams then take steps to safeguard the patient’s well-being in accordance with current recommendations.

We do not include plans for collecting, assessing, reporting, and managing solicited and spontaneously reported adverse events and other unintended effects of trial interventions, as pharmachological treatment is not modified.

### Data analysis

The results are presented following the Consolidated Standards of Reporting Trials (CONSORT) guidelines for randomized controlled trials (RCTs), including extensions for cluster interventions. An initial analysis of the sociodemographic and clinical characteristics of the sample is conducted, and scale scores are calculated.

For the sensitivity analysis, missing data are addressed using the Last Observation Carried Forward (LOCF) imputation method. Additionally, sensitivity analyses are conducted under different assumptions to assess the potential impact of missing data. For both primary and secondary outcome analyses, multivariable linear regression is used to assess differences at 3 and 6 months, with adjustments made based on baseline data to account for any imbalances. Two key assumptions of the regression analysis are tested: the absence of baseline differences between groups and the homogeneity of regression for baseline and six-month follow-up data.

Before conducting the regression analysis, the intracluster correlation coefficient (ICC) is calculated for each outcome, both at baseline and at the six-month follow-up, except for adherence, which is evaluated at both the three- and six-month follow-ups. The ICC is estimated as the ratio of between-subject variance to total variance (between- plus within-subject variance) derived from the ANOVA. This analysis is also applied to the secondary outcomes.

All statistical analyses are performed using SPSS version 21 and Jamovi (IBM, Armonk, NY, United States, RRID).

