## Methods

### Design

This study protocol is a cluster RCT with two parallel arms and single-blind outcome evaluation.

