### Sample size

The sample size estimation account for a 20% difference, as suggested by previous studies conducted in Chile.
^
21
^
^,^
^
22
^ This calculation is based on a one-sided model with an alpha of 5%, a power of 80%, a confidence level of 95%, and a maximum variance of 50%. A total of 240 depressed individuals are required, with 120 participants in each group (intervention and control). Bases on previous data, the intraclass correlation coefficient (ICC) is estimated to be 0.0337,
^
22
^ resulting in a design effect of 1.64 due to the involvement of 12 clinics. Applying this design effect increases the sample size to 341, based on a prior study the sample size is set at 394 patients.
^
8
^

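### The outcome analysis is a patient-level linear regression with no stated method for clinic, although 12 clinics are randomised; at the planning ICC the type I error is roughly 10–17% against a nominal 5%

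*Protocol article*

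**What the plan says.** All references are to the protocol article.

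- **Design:** "This study protocol is a cluster RCT with two parallel arms and single-blind outcome evaluation".
- **Recruitment and randomization:** "Clinics are then assigned to either the intervention or control group using a pseudo-random algorithm". There are twelve clinics, paired on socioeconomic level, adult population and patient income.
- **Sample size:** the calculation uses a "one-sided model with an alpha of 5%, a power of 80"%. On clustering it states that "the intraclass correlation coefficient (ICC) is estimated to be 0.0337", which leads to a design effect of 1.64 and a final size of 394.
- **Data analysis:** for the primary and the secondary outcomes, "multivariable linear regression is used to assess differences at 3 and 6 months", with adjustment for baseline data. An intracluster correlation is to be calculated for each outcome before the regression. It is defined as follows: "The ICC is estimated as the ratio of between-subject variance to total variance (between- plus within-subject variance) derived from the ANOVA". The section then says nothing about what the coefficient is used for. The cluster extension of CONSORT is cited for how results are presented. The regression assumptions to be tested are baseline balance and homogeneity of regression; independence of patients is not among them.

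**The concern.** In its ordinary meaning, multivariable linear regression assumes that patients are independent given the covariates. Patients of one clinic share a team, and here the team is what receives the intervention. Any real difference between clinics therefore adds to the variance of the arm comparison, and a patient-level regression does not count that variance. Its standard errors are too small, its confidence intervals too narrow and its p-values too low. The sample size section recognises this by inflating for clustering; the analysis section does not carry it through.

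The primary PHQ-9 claim and every secondary claim depend on this model. So does a practical decision: the ethics section makes training of the control teams conditional on significantly better outcomes in the intervention arm.

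**Working it through.** **Inputs.** From Sample size: 12 clinics, ICC 0.0337, design effect 1.64, 240 patients before inflation, final size 394, one-sided alpha of 5%. Data analysis gives no sidedness, so both are computed. Assumptions: equal clinic sizes, six clinics per arm, no gain from matching, and a planning ICC that also applies to the analysed scores.

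**1. The plan's own figure.** Design effect DE = 1 + (m − 1) × ICC.
- With m = 240/12 = 20: DE = 1 + 19 × 0.0337 = 1.640, as stated.
- 240 × 1.64 = 393.6, hence 394. (The intermediate 341 does not follow from this product; it is a separate matter and is not used here.)

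**2. Design effect at the size actually planned.**
- m = 394/12 = 32.8, so DE = 1 + 31.83 × 0.0337 = 2.073.
- Ratio of true to naive standard error: √2.073 = 1.44.
- Naive intervals have 1/1.44 = 69% of the width they need before any small-sample correction.

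**3. Type I error of a regression that ignores clinic.** Two-sided: 2 × [1 − Φ(1.96/√DE)]. One-sided: 1 − Φ(1.645/√DE).

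| ICC | Patients per clinic | DE | One-sided 5% test | Two-sided 5% test |
|---|---|---|---|---|
| 0.0337 | 20 (protocol's DE) | 1.64 | 10.0% | 12.6% |
| 0.0337 | 32.8 (394 patients) | 2.07 | 12.7% | 17.3% |
| 0.01 | 32.8 | 1.32 | 7.6% | 8.8% |
| 0.05 | 32.8 | 2.59 | about 15% | 22.3% |

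In the second row, a naive 95% interval covers about 100 − 17.3 = 83%.

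**4. Simulation.** 10,000 trials with no treatment effect, 12 clinics of 33 and ICC 0.0337. Patient-level regression rejected in 17.3% of trials two-sided and 12.7% one-sided. Adding a patient-level baseline covariate left this at 17.3% and 12.6%, so baseline adjustment alone did not repair it. A t test on clinic means with 10 degrees of freedom rejected in 5.1% (5.0% with baseline adjustment).

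**5. The ICC definition.** The section calls the quantity an intracluster coefficient and calculates it at baseline and at six months, yet writes it in terms of between- and within-subject variance. At one visit each patient has one score per outcome, so a within-subject variance cannot be estimated. The quantity that matches the name is between-clinic variance over between- plus within-clinic variance.

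**The case against.** **Silence is not exclusion.** The article gives no full covariate list, calls for an ICC, cites the cluster extension of CONSORT and says that a fuller protocol exists. A reader might infer that the plan rules out any clinic term. The text does not say so; it supports only the statement that no method for clinic is given. That is still enough, because the article does not leave the model open. It names one, and goes into detail down to the variance ratio and the software. An analyst who follows it would fit an ordinary regression, and neither the ICC step nor the CONSORT citation changes the standard errors.

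**The size of the inflation.** A reader might take 17% as the trial's error rate. That figure needs a two-sided test, 32.8 patients per clinic and the planning ICC. The only alpha in the document is one-sided, which gives about 13%, and the protocol's own design effect gives 10–13%. The ICC of baseline-adjusted scores at three and six months is unknown. Effective matching would lower the inflation further, and the simulation has none. All of this stands and is why a range is given. No positive residual between-clinic variance restores 5%.

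**The ICC wording.** Read literally, the definition is a patient's repeatability over visits, and a reader might infer that a very large design effect would enter the analysis. The documents do not support that. The quantity cannot be estimated at a single visit, no repeatability value is given, and the regression makes no stated use of the ICC. A slip for between-clinic is the more plausible reading, so this is a wording correction only.

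**Conclusion.** The concern holds in this form: the model named for all outcomes does not match a clinic-randomised design, and no method for clustering is stated. This is an error in what is written, not a detail left to a later document. At the planning ICC of 0.0337, naive standard errors are too small by a factor of about 1.44 with 394 patients. The type I error is about 13% one-sided or 17% two-sided, or 10–13% with the design effect the protocol itself uses. With an ICC of 0.01 it would be about 8–9%. These figures rest on the assumptions listed with the inputs. They do not show that any particular significant result would be false; they show that the stated test does not hold its stated error rate.

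**What to change.** - **Model.** For the primary and all secondary patient outcomes, replace the regression with a linear mixed model containing arm, baseline score (where one is measured) and a random intercept for clinic, with small-sample degrees of freedom. Alternatively, analyse baseline-adjusted clinic means. State the sidedness of the test.
- **Degrees of freedom.** About 10 (12 clinics − 2 arms) without clinic-level covariates. Including the three matching factors leaves about 12 − 2 − 3 = 7; a pair-based analysis leaves 6 − 1 = 5. The choice should be stated and justified.
- **ICC.** Define it as between-clinic variance over between- plus within-clinic variance, and say that it is reported descriptively.

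**Cost.** At the planning ICC with 10 degrees of freedom, intervals widen by 1.44 × (2.228/1.966) = about 1.63 times: the standard error ratio times the ratio of t quantiles. Honest power is lower than the naive analysis would suggest: 394/2.073 = about 190 independent patients, against the 240 the plan asks for. The Study status section says the trial has concluded, so the change is a re-analysis as well as a wording correction. No new data are needed, since the data carry a clinic code, and SPSS, already named in the plan, can fit the mixed model.

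### The plan tests for absence of baseline differences as if this were a regression assumption, and does not make baseline adjustment unconditional

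*Protocol article*

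**What the plan says.** In the protocol article, under Data analysis, the model for the primary and secondary outcomes is given as "multivariable linear regression is used to assess differences at 3 and 6 months", "with adjustments made based on baseline data to account for any imbalances". The next sentence reads "Two key assumptions of the regression analysis are tested: the absence of baseline differences between groups and the homogeneity of regression", the latter for baseline and six-month data. The section does not list covariates, does not say that the baseline score is in the model whatever the data show, and does not say what is done if the baseline test is significant or not.

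Under Recruitment and randomization, allocation is by clinic: "Clinics are then assigned to either the intervention or control group using a pseudo-random algorithm". Patients are then invited by a member of their own clinic's team. Table 1 shows baseline measurement of the PHQ, GAD-7, OQ-45 and ERS. The adherence scale is measured only at three and six months.

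**The concern.** Baseline adjustment exists because arms can differ at baseline. Treating the absence of such differences as a condition of the regression reverses that logic, and it conflicts with the sentence before it, which adjusts precisely to deal with imbalance. The genuine assumptions of the model concern the form of the regression, the residuals and their dependence within clinic, not equality of the baseline means.

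Because the plan presents the test as a check on the model, an analyst needs to know what to do with the answer. A significant result might be taken to mean that the planned model is invalid or needs further covariates. A non-significant result might be taken to mean that adjustment is unnecessary. Either way the primary model would depend on the observed baseline data. At stake are precision and a clearly defined primary analysis.

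**Working it through.** The plan gives no figure for this point, so there is none to reproduce. The checks below size the consequences.

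**Inputs from the protocol article, Sample size.** ICC: "the intraclass correlation coefficient (ICC) is estimated to be 0.0337". Design effect: "resulting in a design effect of 1.64 due to the involvement of 12 clinics". Total: "based on a prior study the sample size is set at 394 patients".

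**Assumed.**
- A two-sided 5% level for the baseline test. The document gives none; its one-sided 5% belongs to the sample size calculation.
- The planning ICC applies to the baseline scores.
- Six clinics per arm, for items 3 and 4.
- A baseline to follow-up correlation r between 0.3 and 0.7, which the document does not give.

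**1. Precision lost if adjustment is dropped.** Adjusting for a baseline score with correlation r removes a share r² of the residual variance.
- r = 0.3: 0.3² = 0.09, or 9%.
- r = 0.6: 0.6² = 0.36, or 36%.

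**2. False rejection by a patient-level baseline test that ignores clinics.** With design effect DE, the rate is 2 × P(Z > 1.96/√DE).
- Stated DE of 1.64: 1.96/√1.64 = 1.53, rate 12.6%.
- DE at the planned total: 394/12 = 32.8 patients per clinic, DE = 1 + (32.8 − 1) × 0.0337 = 2.07, 1.96/√2.07 = 1.36, rate 17.3%.

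A null simulation with 12 clinics of 33 patients and ICC 0.0337 (2,000 runs per setting) gave 17% to 18%, in agreement. These are rates for the baseline test, not for the treatment comparison.

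**3. What a non-significant clinic-level test would show.** The variance of a clinic mean, in SD² units, is 0.0337 + 0.9663/32.8 = 0.0631. The standard error of the arm difference is √(2 × 0.0631/6) = 0.145 SD. On 10 degrees of freedom, power is about 46% for a true difference of 0.3 SD, and about 0.45 SD is needed for 80%. A non-significant result therefore cannot establish that baseline differences are absent.

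**4. Type I error of the treatment test if adjustment did depend on the baseline test.** The same simulation, analysed at cluster level, compared always adjusting with adjusting only when the baseline test gives p < 0.05.

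| Assumed r | Always adjust | Adjust only if baseline p < 0.05 |
|---|---|---|
| 0.3 | 4.7% | 4.1% |
| 0.5 | 4.7% | 4.9% |
| 0.7 | 5.3% | 4.0% |

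Simulation error is about √(0.05 × 0.95/2000) = 0.5 percentage points. With no clustering, the conditional rule at patient level gave about 4.4%, 4.0% and 3.4% for r = 0.3, 0.5 and 0.7. The departure is small and, where visible, conservative.

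**The case against.** The strongest reply is that no gate is written. The phrase about imbalances can be read as giving the purpose of an adjustment that is always made. The check of homogeneity of regression makes sense only if the baseline score is in the model, so adjustment is probably intended throughout. An article may also leave the handling of a test result to a fuller document. This stands as far as it goes: a reader might infer that the baseline test decides the primary model, but the text supports only that it could. It does not remove the fault, because the listed assumption is wrong as stated and fuller detail elsewhere would not make it right.

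A second reply is that baseline differences here need not be chance. Clinics are randomised, but their own teams invite patients after allocation, so recruitment can differ between arms. This also stands. It would be too strong to call every significant baseline difference a false alarm. It is a reason to report balance carefully; it does not make a significance test a condition of the regression.

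Third, a reader might infer from the 13% to 17% that the trial's type I error is inflated to that level by the baseline test. It is not. Those rates arise only if clinics are ignored, which is a separate matter, and the section does not say how the baseline test is done. Nor can the rate for one score be compounded across the baseline scores as if they were independent, since the same patients report all of them.

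Finally, homogeneity of regression is a genuine assumption of a common-slope model and is not part of the fault.

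**Conclusion.** The point holds in a limited form. The Data analysis section names something that is not an assumption of the regression, proposes to test it, and leaves open what the result would do to the model. Nothing elsewhere in the article corrects this.

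The size is modest. The main cost is the 9% to 36% of residual variance forgone, and it arises only if adjustment is dropped and depends on the assumed correlation. The effect on type I error is slight and mainly conservative, on simulations that assume six clinics per arm. The 13% to 17% false rejection rate applies only to a patient-level test that ignores clinics. The document does not show that adjustment will be dropped or that the primary model will be chosen by a test. The wording is nonetheless wrong and should be corrected, because correcting it is almost free.

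**What to change.** - Delete the test of baseline differences as a regression assumption.
- State that every model for an outcome measured at baseline includes that outcome's baseline score, whatever the observed balance.
- Handle clustering in those models by a random clinic effect or a cluster-level analysis. Fixed clinic effects would be aliased with arm, because each clinic belongs to one arm only.
- Name the covariates for adherence separately, since it has no baseline measurement.
- Report baseline balance by means and standardised differences, without significance tests. This also helps to show differential recruitment after clinics were allocated.
- Keep the homogeneity-of-slopes check as a reported sensitivity analysis that does not decide the primary model.

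The cost is a few sentences. The baseline scores are already in the measurement schedule, so no new data are needed. The article reports that the study has concluded, so the change applies to the analysis and its reporting.

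### The intracluster correlation is defined with the subject, not the clinic, as the class; the definition needs correcting, although no sample size or test in the plan depends on it

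*Protocol article*

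**What the plan says.** The Data analysis section of the protocol article states that, ahead of the regression, "the intracluster correlation coefficient (ICC) is calculated for each outcome, both at baseline and at the six-month follow-up"; for adherence the two visits are three and six months. It then gives the formula: "The ICC is estimated as the ratio of between-subject variance to total variance (between- plus within-subject variance) derived from the ANOVA". The section names no between-clinic or within-clinic variance, and it does not name clinic as the ANOVA factor.

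Two other places show what the cluster is. Under Recruitment and randomization: "Clinics are then assigned to either the intervention or control group using a pseudo-random algorithm". Under Sample size, "the intraclass correlation coefficient (ICC) is estimated to be 0.0337", "resulting in a design effect of 1.64 due to the involvement of 12 clinics".

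**The concern.** An intracluster correlation measures how alike two members of the same cluster are. The clusters here are clinics, so the numerator must be the variance between clinics, and the residual must be the variance between patients of the same clinic. The written formula makes the patient the class and leaves variation within a patient as the residual. That is a repeatability (test-retest) coefficient. The protocol thus plans with one ICC and defines another under the same name.

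This ICC is the only clustering quantity that the Data analysis section computes. If the sentence were followed, the ICC reported for each outcome would either not exist or describe something other than clinics. A comparison with the planning value of 0.0337, or reuse of the figure in a later trial, would then mislead.

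**Working it through.** **Inputs from the protocol.** 12 clinics, 240 patients before inflation for clustering, ICC 0.0337, design effect 1.64 and a final sample of 394 (Sample size); ICC at baseline and six months, or three and six months for adherence (Data analysis); clinic as the unit of randomisation (Recruitment and randomization).

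**Inputs that are assumed.** The protocol gives no correlation between visits and no expected mean change. The correlation r is taken as 0.3, 0.5 and 0.7, and the mean change d as 0 or 1 SD, for illustration only.

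**Step 1: reproduce the plan's own figure.** Design effect = 1 + (m − 1) × ICC, with m = 240/12 = 20. This gives 1 + 19 × 0.0337 = 1.6403, the stated 1.64. The figure comes out with m as patients per clinic, so the planning ICC is a clinic-level correlation.

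**Step 2: set the two definitions side by side.**
- Quantity used for planning: between-clinic variance / (between-clinic + within-clinic, between-patient variance).
- Quantity written in the analysis section: between-subject variance / (between-subject + within-subject variance).

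Variation between patients is the residual in the first ratio and the numerator in the second.

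**Step 3: try the written formula at one visit.** With N patients and one total score each per scale, an ANOVA with patient as the factor has N − N = 0 within-subject degrees of freedom; with 394 patients, 394 − 394 = 0. The ratio cannot be estimated. With clinic as the factor there are 12 − 1 = 11 degrees of freedom between clinics and 394 − 12 = 382 within, so that ratio can.

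**Step 4: see what the written formula would measure if two visits were pooled.** Take total variance 1 at each visit. Then MSB = 1 + r, MSW = 1 − r + d²/2, and the ratio is (MSB − MSW)/(MSB + MSW) = (2r − d²/2)/(2 + d²/2).
- d = 0: the ratio equals r, that is 0.30, 0.50 and 0.70.
- d = 1 SD: (0.6 − 0.5)/2.5 = 0.04; (1.0 − 0.5)/2.5 = 0.20; (1.4 − 0.5)/2.5 = 0.36.

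A simulation of the d = 0 case (12 clinics × 33 patients, true clinic ICC 0.0337, 300 runs per value of r) gave 0.296, 0.500 and 0.697 with patient as the factor. With clinic as the factor at one visit, the mean ICC was 0.036, 0.034 and 0.035. The patient ratio follows the assumed r and d and does not isolate clinic variance; the clinic ANOVA recovers the true value.

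**Step 5: arm at follow-up (secondary).** If the clinic ANOVA at six months ignores arm, a treatment effect enters as clinic variance. For an assumed 0.3 SD arm difference and six clinics per arm, the addition is 0.3²/4 × 12/11 = 0.0245. The apparent ICC becomes (0.0337 + 0.0245)/(1 + 0.0245) = 0.057 in place of 0.0337.

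**The case against.** The strongest reply is that this is a slip of wording. The coefficient is called intracluster, it is scheduled by visit, and the planning calculation uses it at clinic level. All three fit a one-way ANOVA by clinic whose between-group and within-group components were mislabelled as subject variances. Because the literal formula cannot be run at one visit, an analyst would probably have fallen back on the clinic ANOVA. This is plausible, and it means that one cannot say what was or would be computed. It does not rescue the sentence, which uses the wrong unit for both components and names no factor.

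A second reply is that an article leaves detail to the full protocol or the analysis plan. That would answer an omission, but this is an explicit definition, wrongly stated. The reply does hold for arm: the article does not say that arm is left out of the ANOVA, so Step 5 is advice and not an error found.

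A third reply is that nothing depends on the estimate, and this stands. The sample size uses an ICC from earlier data. The Data analysis section states no design-effect correction, variance adjustment or decision rule fed by the computed ICC. A reader might infer from Step 4 that the trial would report ICCs of 0.3 to 0.7, and hence design effects many times 1.64. The documents do not support that: the plan nowhere says that visits are pooled, and those values largely return the assumed correlations. With a 1 SD change and r = 0.3, the pooled ratio of 0.04 is close to the planning value anyway.

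**Conclusion.** The definition is wrong as written. It conflicts with the coefficient's name, with the unit of randomisation and with the protocol's own planning calculation, and it cannot be estimated at the visits stated. These conclusions rest on the text and on Step 1, and need no assumption beyond one total score per patient, scale and visit.

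The consequence is limited to the reported ICC for each outcome and to any check of, or comparison with, 0.0337. No numerical size can be attached, because the documents do not settle which ANOVA is meant; the figures in Steps 4 and 5 are illustrations under stated assumptions. A reader might go further and infer that the trial in fact computed patient repeatability, that the sample size is affected, or that the primary test is biased through this sentence. None of these follows. Whether the regression itself accounts for clinics is a separate question and lends no weight to this one.

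**What to change.** Replace the sentence with one along these lines: *The ICC is the between-clinic variance divided by the sum of the between-clinic and within-clinic (between-patient) variances, estimated separately at each stated visit from a one-way ANOVA with clinic as the factor, within arm (or with arm in the model) at follow-up.*

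The article says that the study has concluded, so the investigators should also confirm that clinic was the factor used and, if it was not, recompute the ICCs before any comparison with 0.0337. The necessary correction is the clinic as the class; the arm clause is a sensible addition. The cost is one sentence and, at most, a rerun of the ICC calculation on existing data. Sample size, visits and the regression are unchanged.
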